#### Reporting

The PI will report any incidents, i.e., adverse events (AEs) or serious adverse events (SAEs), that meet the Office for Human Research Protections (OHRP) criteria for unanticipated problems. The PI will complete a form with the following information to the IRB: (1) appropriate identifying information for the research protocol (i.e., title, investigator’s name, IRB project number); (2) a detailed description of the adverse event, incident, experience, or outcome; (3) an explanation of the basis for determining that the adverse event, incident, experience, or outcome represents an unanticipated problem; and (4) a description of any changes to the protocol or other corrective actions that have been taken or are proposed in response to the unanticipated problem. Unanticipated problems that are serious adverse events will be reported to the IRB, IMC, and National Center for Complementary and Integrative Health (NCCIH) within 7 days, and any other unanticipated problem will be reported within 14 days of the investigator becoming aware of the problem/event. All unanticipated problems should be reported to the appropriate institutional officials (as required by an institution’s written reporting procedures), the supporting agency head (or designee), and the OHRP within 1 month of IRB’s receipt of the report of the problem from the investigator.

Study progress and safety will be reviewed monthly (and more frequently if needed). Progress reports, including patient recruitment, retention/attrition, AEs, and SAEs, will be provided to the IMC semi-annually. An annual report will be compiled and will include a list and summary of AEs and SAEs and will address (1) whether AE/SAE rates are consistent with pre-study assumptions, (2) the reason for dropouts from the study, (3) whether all participants met entry criteria, (4) whether continuation of the study is justified on the basis that additional data are needed to accomplish the stated aims of the study, and (5) the conditions whereby the study might be terminated prematurely. The annual report will be sent to the IMC and will be forwarded to the IRB and NCCIH. The IRB and other applicable recipients will review progress of this study on an annual basis. The study team will generate study reports for the IMC and will provide information on the following study parameters: enrollment status, subject status, demographics, stopping or halting rules, unanticipated problems, adverse events, protocol deviations, quality management, and outcome data (if applicable at time of report). Study report tables will be generated only from aggregate (not by group assignment) baseline and aggregate safety data for the study population.

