The study will be stopped prior to its completion based upon (1) clinical deterioration of PTSD symptomology (increased scores of >20 points from baseline on the Impact of Event Scale-Revised (IES-R) in >50% of the enrolled participants), (2) difficulty in study recruitment (i.e., at halfway through the timeline of recruitment, study recruitment falls below 30% of the total recruitment goal), and (3) if any new safety information or research becomes available during the trial that necessitates stopping.

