### Allocation (phase 2 only)

Block randomization will be used to assign participants to treatment groups. Specifically, the biostatistician will construct 15 blocks of six participants using SAS PROC PLAN with a random number seed known only by the biostatistician. This will be done at the beginning of the study (front-loaded) and provided to a research staff member not associated with this study (i.e., trusted broker). The trusted broker will utilize the treatment allocations to sequentially assign enrollees to randomized treatment groups (the biostatistician will be shielded from enrollment date and enrollment order, and participant IDs will not reflect enrollment order). The trusted broker will hold the codes that match participants to treatment groups. Research staff members will call the trusted broker to determine assignment to group. In case of adverse events (AE), the research staff member will call the trusted broker to provide for unblinding (AE only). After randomization, participants will be emailed a study information packet (i.e., instructions, UDAYA username/password) according to the intervention assigned. The initiation of the study will begin after allocation to study arm (see Fig. 2 for phase 2 study flow chart).

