### Blinding (phase 2 only)

The principal investigator and biostatistician will remain blinded until the completion of data collection (i.e., data is locked). Following the conclusion of data collection (i.e., data is locked), the biostatistician will be unblinded as data analysis will require knowledge of treatment assignment. The study coordinator and graduate student worker that deliver the intervention(s) and prepare reports to the Independent Monitoring Committee (IMC) will be unblinded. The study coordinator will be responsible for the intervention groups, and the graduate student worker will be responsible for the control group. A research staff not directly involved in the study will serve as the “trusted broker” to handle the sequential assignment of participants to randomized treatment groups and will also be unblinded.

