#### Adverse events

An AE is any untoward medical occurrence in a subject during participation in the clinical study or with use of the experimental agent being studied. An adverse finding can include a sign, symptom, abnormal assessment (laboratory test value, vital signs, electrocardiogram finding, etc.) or any combination of these regardless of relationship to participation in the study. Adverse events that are non-serious will be provided to the IMC with summaries of the numbers and rates of AEs by group.

Expedited review will occur for all events meeting the FDA definition of serious adverse events (SAEs), i.e., any fatal event, immediately life-threatening event, and permanently or substantially disabling event. This also includes any event that a study investigator or the IMC judges to impose a significant hazard, contraindication, side effect, or precaution. For purposes of this study, all SAEs will be reported to the IMC regardless of any judgment of their relatedness to the study treatment.

The PI will record all reportable events with start dates occurring any time after informed consent is obtained until 7 (for non-serious AEs) or 30 days (for SAEs) after the last day of study participation. Each week, participants will report in their weekly logs the occurrence of AE/SAEs since the last week. If the participants are not completing their logs, they will be prompted via email by the research team to complete their logs. If there are two consecutive failed email attempts, the participants will be called. Events will be followed for outcome information until resolution or stabilization.

The research team will determine if the event is an AE or an SAE. If an SAE, the research team will complete a form to be provided to the IMC to meet and investigate the SAE until determined resolved or stable and its relation to the study (related or not related). Once recruitment begins, IMC will meet twice a year and will meet ad hoc when AE or an SAE occur. AE reports and annual summaries will not include individual identifiable private information about the human subjects. Each report will only include the identification code previously assigned.

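### The protocol promises the monitoring committee adverse event rates by group in one section and restricts its report tables to aggregate data in another; the two must be reconciled

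*Protocol article*

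**What the plan says.** Four places in the protocol article bear on what the IMC sees.

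- **Adverse events** (under Data monitoring): "Adverse events that are non-serious will be provided to the IMC with summaries of the numbers and rates of AEs by group". For serious events, "all SAEs will be reported to the IMC regardless of any judgment of their relatedness to the study treatment". The arm is not mentioned for serious events.
- **Reporting**: "The study team will generate study reports for the IMC and will provide information on the following study parameters". The list that follows includes adverse events. The section then closes with "Study report tables will be generated only from aggregate (not by group assignment) baseline and aggregate safety data for the study population".
- **Blinding (phase 2 only)**: "The study coordinator and graduate student worker that deliver the intervention(s) and prepare reports to the Independent Monitoring Committee (IMC) will be unblinded". The principal investigator and the biostatistician stay blinded until the data are locked.
- **Allocation (phase 2 only)**: "In case of adverse events (AE), the research staff member will call the trusted broker to provide for unblinding (AE only").

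The Adverse events section also has participants complete the IES-R at 6 weeks, with one item on whether they think the intervention is contributing to their symptoms. Both are for the IMC to review. The format of that review is not stated.

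**The concern.** The Adverse events and Reporting sections give opposite instructions for the same kind of data going to the same committee. One calls for adverse event rates by group. The other uses the word only and rules out tables by group. Whoever prepares an IMC report has no stated basis for choosing between them.

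The choice matters because the trial compares two yoga doses and an exercise control in women who enter with IES-R scores of at least 33. Symptoms and distress are therefore to be expected in every arm. A pooled event rate has no internal comparator, so it cannot show whether one arm is doing worse than the others, and a one-arm excess is diluted by the two unaffected arms.

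**Working it through.** The protocol states no adverse event rate, so there is no figure to reproduce. The check has two parts: a comparison of the texts, and a calculation of what pooling does.

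**1. Texts compared**

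| Question | Adverse events section | Reporting section |
|---|---|---|
| Recipient | IMC | IMC |
| Data | non-serious adverse events, numbers and rates | study report tables: baseline and safety data, with adverse events among the listed contents |
| Level | by group | aggregate, explicitly not by group |
| Exception or precedence | none stated | none stated |

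The recipient is the same, the adverse event content overlaps, and the level of detail is opposite. The Blinding section says that those who "prepare reports to the Independent Monitoring Committee (IMC) will be unblinded". Tables by arm could therefore reach the committee without unblinding the principal investigator or the biostatistician.

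**2. Dilution if the aggregate rule governs**

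Input from the protocol: 90 women, 30 per arm (Study design, Phase 2). Assumption: the event rates below, which are illustrations only.

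Let *b* be the event rate in the two unaffected arms and *h* the rate in the affected arm.

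- Pooled rate = (30*b* + 30*b* + 30*h*)/90 = (2*b* + *h*)/3
- Pooled excess over background = (2*b* + *h*)/3 − *b* = (*h* − *b*)/3

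The factor of one third follows from equal allocation and holds for any rates.

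| *b* (assumed) | *h* (assumed) | True excess | Pooled rate | Pooled excess |
|---|---|---|---|---|
| 5% | 20% | 15 points | (5+5+20)/3 = 10.0% | 5.0 points |
| 5% | 30% | 25 points | (5+5+30)/3 = 13.3% | 8.3 points |
| 10% | 30% | 20 points | (10+10+30)/3 = 16.7% | 6.7 points |
| 10% | 40% | 30 points | (10+10+40)/3 = 20.0% | 10.0 points |

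The last column overstates what the committee could learn. In a pooled table *b* is unknown, so the committee sees 16.7% and cannot tell whether that is background.

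**3. What tables by arm would add at this size**

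For the same assumed examples with full arms (Fisher's exact test, two-sided):

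- 9/30 against 3/30 (30% against 10%): p = 0.10
- 9/30 against the other two arms combined, 6/60: p = 0.03
- 12/30 against 3/30 (40% against 10%): p = 0.015

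Tables by arm would thus make a large one-arm excess visible, and a moderate one only weakly. The semi-annual IMC reports during enrollment would rest on fewer women.

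**The case against.** The strongest reply is that the two sections may describe different documents: an adverse event summary by group, and a general study report on enrollment, demographics, deviations and quality management. The general report is described next to an annual report that goes on to the IRB and the funder. Both could then be followed. The Research ethics approval section also mentions data and safety monitoring plans, which are not shown and may set out such a split. This reading is workable, but the article does not state it. The Reporting section names the IMC as recipient and adverse events as content, so the text as published still conflicts.

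A reader might go further and infer any of four things that the documents do not support.

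- *That the plan hides one-arm harm from the committee.* It does not fix this. The Adverse events section already provides rates by group for non-serious events; the loss occurs only if the Reporting rule overrides it.
- *That tables are the committee's only view of harm.* Every serious event goes to the IMC, which investigates its relation to the study and also meets ad hoc when events occur. Allocation can be unblinded for adverse events through the trusted broker. There is the participant's own attribution item at 6 weeks, and the PHQ-9 is collected every 2 weeks and monitored daily. These are real safeguards for individual cases, but none gives rates by arm.
- *That the 6-week IES-R will be seen only pooled.* The protocol says it is for IMC review and does not say in what form. The aggregate rule refers to baseline and safety data and does not name this measure.
- *That the deterioration stopping rule makes this point more serious.* That rule requires "increased scores of >20 points from baseline on the Impact of Event Scale-Revised (IES-R) in >50% of the enrolled participants", so it is counted across arms whatever tables the committee receives. It is a separate matter and adds no weight here.

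**Conclusion.** The contradiction stands. The article tells the study team both to give the IMC adverse event rates by group and to build its report tables only from aggregate data, and nothing shown reconciles the two. The consequence is conditional: if the aggregate rule is followed, the committee has no comparative adverse event rates, and an excess in one arm appears at one third of its size. The one-third factor rests only on the 30:30:30 allocation. The example of 16.7% rests on assumed rates of 10%, 10% and 30%.

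This should be fixed as an internal inconsistency on safety reporting. A higher grade is not justified, because one of the two passages already provides group-level reporting for non-serious events and individual review is extensive. No estimand, sample size or efficacy analysis changes.

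**What to change.** Amend the closing sentence of the Reporting section so that the aggregate-only rule applies to reports reaching the blinded principal investigator, the IRB and the funder. State there that the IMC receives summaries of adverse events and serious adverse events by arm, with coded arm labels if preferred, prepared by the staff already unblinded under the Blinding section.

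The by-group sentence in the Adverse events section covers non-serious events only. Serious events by arm must therefore be added expressly; making the two sections agree would not bring them in. Giving the committee the 6-week IES-R by arm as well is preferable, since that measure is collected for its review, but this goes beyond resolving the contradiction.

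The cost is a sentence or two of text and one extra table per IMC report. No new data or staff are needed, and the principal investigator and biostatistician stay blinded provided the tables by arm go to the IMC alone. The change should be in place before the first IMC report. If the approved data and safety monitoring plan already separates the two kinds of report, a cross-reference to it in the Reporting section would be enough.

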### Research ethics approval

The Arizona State University Institutional Review Board has approved all protocols, data and safety monitoring plans, and study materials. All protocol amendments, other than minor administrative changes as defined by the NCCIH Guidance on Changes in Clinical Studies in Active Awards, will be submitted in a prospective manner to NCCIH except when necessary to protect the safety, rights, or welfare of subjects. Prior to submission to NCCIH, the proposed changes will be reviewed and approved by the IMC. IRB approval will not be sought until after NCCIH approval of the protocol amendment has been obtained.

### Informed consent

All consent documents will be obtained electronically, via Qualtrics, prior to the woman’s participation in the study (phase 1 or phase 2). The consent form will describe the purpose of the study, the procedures to be followed, and the risks and benefits of participation. A PDF copy will be emailed to the participants at their request.

### Timeline

See Table 5 for project timeline.

**Table 5 Tab5:** Project timeline

Item	Year 1—months						Year 2—months						Year 3—months					
	1–2	3–4	5–6	7–8	9–10	11–12	13–14	15–16	17–18	19–20	21–22	23–24	25–26	27–28	29–30	31–32	33–34	35–36
Hire research personnel	X	X																
Continue to engage non-for profit partnerships		X	X	X	X	X												
Finalize manual of procedures for all protocols		X	X															
Finalize participant materials			X															
Finalize control group prescription				X														
Finalize Udaya yoga prescription				X														
Develop recruitment plans and materials				X	X													
Train research staff on study rocedures					X													
Modifications to Udaya.com (i.e., fidelity tracking, filming control group sessions)			X	X	X													
Obtain IRB approval						X												
Recruitment and enrollment							X	X	X	X								
Baseline data collection							X	X	X	X	X							
Post data collection								X	X	X	X	X						
Follow-up data collection									X	X	X	X	X					
Data analysis										X	X	X	X	X	X	X		
Manuscript preparation											X	X	X	X	X	X	X	X
Grant preparation										X	X	X	X	X	X	X	X	X

## Discussion

This RCT study will explore the feasibility and acceptability of a 12-week, home-based, online-streamed yoga intervention, with varying doses (low = 60 min/week; moderate = 150 min/week) among bereaved mothers who have experienced a stillbirth within 6 weeks to 24 months. To date, this is the first study to ascertain the preliminary effects of home-based, online-streamed yoga on reducing PTSD symptoms below the clinical threshold in mothers who have experienced the death of a baby to stillbirth. This study is particularly important not only because the risk for PTSD is nearly seven times the risk as compared to that for mothers with live births but also because there have only been two randomized control trials in the last 30 years aimed at improving emotional and mental health in these grieving mothers, which also affects surviving and subsequently born children. If feasible, the findings from this study will inform a full-scale trial to determine the effectiveness of home-based, online-streamed yoga to improve PTSD. Long-term, health care providers could use online yoga as a non-pharmaceutical, inexpensive resource to help women manage their symptoms after a stillbirth.

## Abbreviations

AE: Adverse event
ER: Emergency room
ERQ: Emotional Regulation Questionnaire
HIPAA: Health Insurance Portability and Accountability Act
IES-R: Impact of Event Scale-Revised
IMC: Independent Monitoring Committee
IRB: Institutional Review Board
LD: Low dose
MAAS: Mindful Attention Awareness Scale
MD: Moderate dose
NCCIH: National Center for Complementary and Integrative Health
NIH: National Institutes of Health
PGS: Perinatal Grief Scale
PHQ-9: Patient Health Questionnaire-9
PSQI: Pittsburgh Sleep Quality Index
PWMAQ: Past-week Modifiable Activity Questionnaire
RCT: Randomized controlled trial
SAE: Serious adverse event
SCS: Self-Compassion Scale
STAI: State-Trait Anxiety Inventory
STC: Stretch and tone control
